### Primary endpoint

The primary efficacy objective of this study is to assess the impact of optimized HF therapy on self‐care ability and self‐reported health status in terminal cancer patients receiving palliative care. The primary hierarchical endpoint (to be analysed by the win ratio) has the following components: (1) days alive and being able to wash themselves, (2) the ability to walk 4 m, and (3) the self‐reported patient global assessment (PGA) of subjective well‐being during 30‐day period to the end of placebo‐controlled phase.

For the first component ‘days alive and being able to wash themselves’, any method for washing (shower, bath, sink, or sponge bath in bed) will be considered during the 30‐day period to the end of the placebo‐controlled phase (up to the visit of day 30 [30 ± 2 days after the baseline visit]), with the counts ranging from 0 to 32 days. A higher number (or higher proportion) of days will determine the ‘win’, if the difference between two patients being compared exceeds 1 day (or an equivalent proportion). For cases when both patients survive the entire placebo‐controlled phase, then only the period of time of the patient with shorter observation time will be considered (i.e. day 28–32 or the related visit). If only one of the two patients compared reached the final assessment day and the withdrawal of the second patient is considered independent of disease severity (in blinded assessment), the shared observation time (i.e. to the end of study for the patient with shorter observation time) is considered. If only one of the two patients compared reached the final assessment day and the withdrawal of the second patient is considered dependent on disease severity, this person is considered unable to wash themselves, to not being able to walk, and to consider their health ‘much worse’ in PGA until the end of study (i.e. the visit on day 30).

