If neither of the patients complete their study period (due disease progression [i.e. entering the dying process] or death), an imputed observation time (day 30) will be used to assess the outcome for both patients. For patients with documented disease progression related study withdrawal, a worst‐case imputation will be performed, i.e. patients will be considered unable to wash themselves, unable to walk, or considered their health ‘much worse’ in the PGA. If precise day‐by‐day recorded data are not available for both patients, and results for the observation period are only provided as summary statistics at visit‐day 10, visit‐day 20, and visit‐day 30, then results will be calculated up to the end of their last common visit on day 10, 20, or 30, respectively, using the ‘last common visit’ approach. Under the ‘last common visit’ approach, the win criterion for the percentage of days alive and able to wash oneself is defined as a difference between two patients of >15.00% for an observation period extending to visit‐day 10, >10.00% for visit‐day 20, or >5.00% for visit‐day 30, with the patient demonstrating the higher percentage deemed the winner.

The second endpoint component, i.e. the ‘ability to walk 4 m’ (during 30‐day intervention phase), will be assessed at days 10, 20, and 30, with counts ranging from 0 to 3 visits. The patient with a higher number will be the ‘winner’. The walking ability is measured by the time taken to walk 4 m, with timing starting from the first foot movement and ending when one foot crosses the finishing line. The result is also used to calculate walking speed. For patients who die or are unable to walk, the walking speed will be recorded as zero.

The third component of the primary endpoint, i.e. ‘self‐reported PGA of subjective well‐being’, will be assessed at the last common assessment visit where both patients were alive (i.e. day 30, 20, or 10). The PGA assesses overall well‐being since enrolment on a 7‐point Likert scale ranging from ‘much worse’ to ‘much improved’. For patients who died, a value (8) ‘dead’ will be assigned. A better PGA score will be considered a ‘win’ but only if it is better than at least score of 6 (i.e. a patient needs to at least ‘moderately worse’). Pre‐specified sensitivity analyses for this win ratio include introducing all‐cause mortality as the highest‐priority component, where longer survival wins with a difference exceeding one day, and reversing the order of walking and PGA components.

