**Primary endpoint (assessed in the controlled treatment phase)**
Win ratio hierarchical endpoint:
Days alive and able to wash themselves since baseline during 30 days of follow‐up to the end of the placebo‐controlled phase, with counts ranging from 0 to 32 days.^a^, ^b^
*Note 1: Definition of ‘washing themselves’: patient performed act of washing by themselves without interference of staff, regardless of whether as shower or bath, on a sink, or using a ‘sponge bath’ in the bed*.
*Note 2: Higher number of days (or proportion of days) will be counted as win, if the difference is >1 day (or a equivalent proportion)*.
2 Number of days alive and able to walk 4 m, assessed up to three times (days 10, 20, and 30), with counts ranging from 0 to 3 days.
*Note 1: Walking ability and time are assessed starting in a still standing position – timing starts with the first foot movement and ends when one foot completely crosses the 4 m‐finishing line. Times are used to calculate walking speed (see also other secondary endpoints). If a patient has not completed the 4 m walking distance within 60 s, the patient is considered not being able to walk 4 m and the related speed is set at zero*.
*Note 2: Higher number of days will be counted as win*.
3 PGA of well‐being during the 30‐day period to the end of the placebo‐controlled phase (7‐point Likert scale).
*Note: Better PGA score counts as win, but only if the winning score is better than ‘much worse’*.

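### Two win thresholds of the primary endpoint are internally inconsistent: the day-20 washing margin departs from the more-than-1-day rule, and the PGA cut-off is stated in two incompatible ways

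*Protocol article*

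**What the plan says.** **Washing, general rule.** In the protocol article, Methods, Primary endpoint, the patient with more days wins "if the difference between two patients being compared exceeds 1 day (or an equivalent proportion"). Table 3, component 1, Note 2 repeats this: "if the difference is >1 day (or a equivalent proportion").

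**Washing, fallback rule.** If daily records are missing and "results for the observation period are only provided as summary statistics at visit‐day 10, visit‐day 20, and visit‐day 30", each pair is compared up to its last common visit. The win margin on the percentage of days is then ">15.00% for an observation period extending to visit‐day 10, >10.00% for visit‐day 20, or >5.00% for visit‐day 30". The day-30 visit falls at "30 ± 2 days after the baseline visit", and Table 2 gives the same ±2 days for the other intervention-phase visits.

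**PGA.** In the Primary endpoint text, the better score wins "only if it is better than at least score of 6 (i.e. a patient needs to at least ‘moderately worse"). Table 3, component 3, says: "Better PGA score counts as win, but only if the winning score is better than ‘much worse". The scale has seven points, and the text adds an eighth code: "For patients who died, a value (8) ‘dead’ will be assigned".

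**The concern.** These rules decide whether a pair is a win, a loss or a tie in the primary analysis. The general washing rule claims that days and proportions are equivalent, yet the three fallback percentages do not correspond to one common number of days. The washing rule also counts twice: the Statistical analysis section applies specific criteria for aggregated washing data to the washing-days endpoint, which is the gate to the other four key secondary endpoints.

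For the PGA the problem is ambiguity. The sentence in the text and the note in Table 3 cannot both be programmed, because they classify one pair of scores differently.

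**Working it through.** **Inputs.** General margin: more than 1 day (Primary endpoint; Table 3). Fallback margins: 15%, 10% and 5% at days 10, 20 and 30 (Primary endpoint). Visit window: ±2 days (Table 2). Code 8 for death (Primary endpoint). Assumptions: days are whole numbers, and both patients in a pair have the same number of observed days, d.

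**Step 1: margins in days.** Margin = percentage × d.
- Day 10: 0.15 × 10 = 1.5 days
- Day 20: 0.10 × 20 = 2.0 days
- Day 30: 0.05 × 30 = 1.5 days

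**Step 2: smallest winning difference at nominal days.** This is the smallest whole k with k/d above the margin.
- Day 10: 1/10 = 10% fails, 2/10 = 20% wins, so 2 days
- Day 20: 2/20 = 10% is not above 10%, 3/20 = 15% wins, so 3 days
- Day 30: 1/30 = 3.33% fails, 2/30 = 6.67% wins, so 2 days
- General rule: more than 1 day, so 2 days

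**Step 3: across the visit windows.**

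| Visit | Days observed | Margin in days | Smallest win |
|---|---|---|---|
| 10 | 8 to 12 | 1.2 to 1.8 | 2 days throughout |
| 20 | 18, 19 | 1.8, 1.9 | 2 days |
| 20 | 20, 21, 22 | 2.0, 2.1, 2.2 | 3 days |
| 30 | 28 to 32 | 1.4 to 1.6 | 2 days throughout |

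So the same 2-day difference wins at 18 observed days (2/18 = 11.1%) and ties at 20 (10.0%) or 22 (9.1%).

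**Step 4: which fixed margins reproduce the general rule?** One day must never win and two days must always win. The margin must therefore be at least 1/(shortest d) and below 2/(longest d).
- Day 10: from 1/8 = 12.5% to below 2/12 = 16.7%; 15% lies inside
- Day 20: from 1/18 = 5.56% to below 2/22 = 9.09%; 10% lies outside
- Day 30: from 1/28 = 3.57% to below 2/32 = 6.25%; 5% lies inside

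A 1.5-day margin at day 20 is 1.5/20 = 7.5%, which lies inside. The literal 1-day proportion, 1/20 = 5%, does not: at 18 observed days a single day (5.56%) would already win.

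**Step 5: PGA.** With 8 for death above a seven-point scale, 7 is 'much worse'; the gloss then makes 6 'moderately worse' (inferred). For two living patients with scores 1 to 7:
- Literal text: the winning score must be 5 or better
- Gloss and Table 3: the winning score may be 6

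Listing all ordered pairs under both rules, the only one that changes is 6 versus 7.

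**Step 6: sample size.** The stated power (29 completers per arm, difference 5, SD 6, two-sided 0.05) reproduces: 86.1% from the t-test with efficiency 3/π, 85.9% by simulation and 83.4% by Noether's formula, against the article's 85%, 86.4% and 83.4%. For the win ratio of 2.1 with 10% ties, 92 patients give 79.6%, against the stated 80%. Neither calculation uses the washing margins or the PGA cut-off.

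**The case against.** The best defence is that the fallback percentages are a criterion of their own. The article does not call them 1-day equivalents, and none is: the exact proportions would be 10%, 5% and 3.33%. An evenly stepped 15/10/5 scale may be deliberate, and >10.00% is explicit, so it can be programmed in only one way. On the PGA, the sentence is visibly garbled and its gloss agrees with Table 3, so the intent is fairly clear. Both rules also treat the arms alike.

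Much of this stands. A reader might infer that 10.00% is a proven slip; the article does not establish that. Nor does the washing margin lead two programmers to different results; only the PGA wording does. What does not stand is that the scale is coherent. In days it runs 1.5, 2.0, 1.5, no reason is given, and only day 20 departs from the general rule.

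Two stronger readings should also be set aside.
- A reader might add 6-versus-8 pairs to the PGA problem. The text takes the PGA at the last common visit with both patients alive, so such pairs should not arise.
- A reader might put a figure on the share of all pairs affected by the day-20 margin. That needs a survival curve and a rate of missing daily records, neither of which is given. It must also allow for the rules that carry severity-related withdrawals, and pairs in which neither patient completes, to day 30.

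**Conclusion.** Both inconsistencies are real, narrow and located in the primary endpoint definition. The washing inconsistency concerns only fallback pairs scored at day 20, with 20 to 22 observed days and a difference of exactly 2 days. Such a pair passes to the walking and PGA stages instead of being decided on washing. The PGA inconsistency concerns only pairs that reach the third stage with scores of 6 and 7.

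The number of such pairs cannot be derived from the article. As an illustration only, about 9% of pairs compared over 20 days would differ by exactly 2 days if counts were uniform on 0 to 20 (2 × 19/441 = 8.6%). The figure is about 11% under rounded normal counts with the planned means of 11 and 16 and SD 6, scaled to 20 days. These are shares of an unknown number of fallback pairs, not of all pairs.

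The effect on the result is probably small. No directional bias or inflation of Type I error is shown, and the stated sample size and power are unaffected. The case for correction is that thresholds deciding the primary test should agree with each other.

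**What to change.** **Washing.** Replace the day-20 margin with a value that reproduces the more-than-1-day rule throughout 18 to 22 observed days. One such value is >7.50%, which matches the 1.5-day margins at the other two visits. If 10.00% was deliberate, say so, drop the claimed equivalence for the fallback, and report the >7.50% version as a sensitivity analysis.

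**PGA.** State one rule in both the Primary endpoint text and Table 3: the winning score must be 6 or better, that is, better than 'much worse'. Delete the phrase requiring a score better than 6.

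**Timing and cost.** Make both corrections before unblinding. The article does not say whether unblinding has taken place; if it has, report the primary analysis under both readings. The cost is two sentences and the matching lines of the win-rule program. No further data are needed.

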### Statistical analysis

Descriptive statistics will summarize qualitative categorical variables with count and percentage and quantitative variables with mean, standard deviation, median, quartiles, and range. Before statistical analysis, a blinded data review will be conducted to identify protocol deviations that may affect study outcomes. Protocol deviations, potential outliers, and missing data will be evaluated following the International Conference on Harmonization (ICH) E9 guidelines.^31^ The primary endpoint will be tested two‐sided at a significance level of 0.05, focusing on a hierarchical composite outcome: stage 1 (days alive and able to wash themselves since baseline), stage 2 (number of days alive and able to walk 4 m), and stage 3 (PGA of well‐being).

Key secondary endpoints will only be tested if the primary hypothesis is rejected, with multiplicity adjustment for the five key secondary endpoints performed hierarchically: first, the ‘washing days’ endpoint will be tested at 5% significance, and if rejected, the additional four key secondary endpoints (number of days alive and being able to walk 4 m, PGA of well‐being, overall quality of life [EORTC QLQ‐C15‐PAL question 15], and NT‐proBNP during the 30‐day intervention phase) will be tested using the Hochberg procedure^32^ at 5% significance to control the familywise Type I error rate. All other endpoints will be tested at a nominal two‐sided significance level of 5%. Deceased patients or patients who withdrew from the study (dependent on/independent of disease severity) will be imputed in the analysis. Primary approach taken in the analysis for longitudinal data with follow‐up truncated by death is unconditional; for example, a deceased patient is assigned a worst‐case value (e.g. a PGA value of 8, a walking speed of 0, an ECOG value of 5, a Karnofsky index of 0, and a PPS of 0) or the last observation is carried forward, respectively, if imputation is required.

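### In the primary win ratio, the PGA tier is read only while both patients are alive, so the assigned score for death cannot enter; the washing-days fallback also drops days lost to death

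*Protocol article*

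**What the plan says.** All references are to the Protocol article.

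- **Primary endpoint, third tier.** PGA "will be assessed at the last common assessment visit where both patients were alive (i.e. day 30, 20, or 10". Then, in the same paragraph: "For patients who died, a value (8) ‘dead’ will be assigned". A better score wins only if it is better than the worst living category (Primary endpoint; Table 3).
- **Statistical analysis.** The primary approach to longitudinal follow-up "truncated by death is unconditional", and "a deceased patient is assigned a worst‐case value (e.g. a PGA value of 8, a walking speed of 0" and so on. The same sentence also allows the last observation to be carried forward where imputation is needed.
- **Primary endpoint, withdrawal.** A patient whose withdrawal is judged related to disease severity, compared with a completer, is scored as unable to wash, unable to walk and in the worst PGA category up to the day-30 visit.
- **Primary endpoint, neither patient completes.** Day 30 is imputed as the observation time for both.
- **Primary endpoint, washing fallback.** "If precise day‐by‐day recorded data are not available for both patients" and only visit summaries exist, "then results will be calculated up to the end of their last common visit on day 10, 20, or 30". The win margin is more than 15%, 10% or 5% for the three horizons.
- **One death and one completer.** The text for pairs with one completer speaks of withdrawal only. Footnote a of Table 3 says that the specific follow-up time is used. Neither states a rule for death.

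**The concern.** The two PGA rules sit in one paragraph and give different winners. Programmers working from this text could score the same pair in opposite directions, in the one confirmatory test on which all key secondary tests depend. Under the both-alive rule a death between visits leaves the last living score standing, while a severity-related withdrawal is set to the worst living score to day 30. Death is then scored more kindly than withdrawal.

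The fallback has a related fault. Its tier is named for days alive and able to wash, yet days lost to death after the last common visit do not count. When neither patient completes, the main rule counts to day 30. In a population with an expected survival of one to six months, pairs with one death will be common. A choice made once the allocation is known could look driven by the result.

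**Working it through.** **1. The plan's own figures.** The power statements reproduce and do not depend on how death is scored.

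- Wilcoxon, 58 completers, index 0.278: Φ(√(12 × 0.25 × 58) × |0.278 − 0.5| − 1.96) = 83.4%, as stated for nQuery.
- Win ratio 2.1, ties 10%, 92 patients: Φ(√(92 × 3 × 0.25 × 0.9 / (4 × 1.1)) × ln 2.1 − 1.96) = 79.6%, against 80% stated.

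**2. PGA tier, one pair (1 = best).** A and B never wash or walk, so tiers 1 and 2 tie. A dies on day 25. Day-20 PGA is 3 for A and 5 for B, and B is still at 5 on day 30.

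- Last visit with both alive (day 20): 3 against 5, so A, who died, wins.
- Day 30 with 8 for death: 8 against 5, so B wins.
- Had A died before day 10, the first rule would have no visit to use.

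**3. Washing fallback, two pairs.**

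| Pair | To last common visit | To day 30 |
|---|---|---|
| A 20/20, dies day 21; B 16/20 then 10/10 | 100% v 80%; 20% > 10%: A wins | 20/30 = 66.7% v 26/30 = 86.7%; 20% > 5%: B wins |
| A 10/10, dies day 11; B 8/10 then 20/20 | 100% v 80%; 20% > 15%: A wins | 10/30 = 33.3% v 28/30 = 93.3%; 60% > 5%: B wins |

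**4. How often it could matter: simulation.** The inputs are assumptions, not document figures. A shared frailty term links death, washing, walking and PGA; 40,000 pairs of one decedent and one survivor were drawn per scenario. With no common visit, the visit-based tiers were scored as ties. Entries are decedent wins as a percentage of such pairs, with the part won in the PGA tier in brackets.

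| 30-day mortality | Washing to day 30, PGA 8 for death | Washing to day 30, both-alive PGA | Fallback washing, both-alive PGA |
|---|---|---|---|
| 11.2% | 19.7 (0) | 20.5 (0.79) | 25.4 (1.65) |
| 21.8% | 18.7 (0) | 19.5 (0.80) | 24.5 (1.67) |
| 31.8% | 17.7 (0) | 18.4 (0.70) | 23.8 (1.64) |
| 41.4% | 16.7 (0) | 17.3 (0.65) | 22.6 (1.50) |

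With daily data (middle column), multiplying by the share of pairs with exactly one death (20.0% to 48.5%) gives 0.79% × 0.200 = 0.16% up to 0.65% × 0.485 = 0.32% of all pairs.

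**5. Limit from the planning figures.** The plainest route to the PGA tier is two patients with no washing day and no walking visit. For a non-negative count with mean 11 and SD 6 (Sample size calculation), the one-sided Chebyshev (Cantelli) bound on the share at zero is 36 / (36 + 121) = 22.9%. A normal approximation gives Φ((0.5 − 11)/6) = Φ(−1.75) = 4.0%.

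If a share p scores zero on both tiers and 40% of these die (an assumption), pairs with exactly one death are 2 × 0.4 × 0.6 × p² = 0.48p²: 1.9% of all pairs at p = 20%, and 2.5% at the bound. If deaths in that group were 60% against 30%, the net shift at p = 20% is (0.6 × 0.7 − 0.4 × 0.3) × 0.04 = 1.2% of pairs. With no other effect, the win ratio would be about 0.98 with death ranked worst and 1.00 under the both-alive rule.

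**The case against.** A reader might infer that the primary endpoint does not penalise death at all, or that it is blind to excess mortality. The document does not support that. Tier 1 counts days alive and able to wash, tier 2 counts visits alive and able to walk (Table 3), and day 30 is imputed when neither patient completes. Mortality is a safety endpoint with Cox and Kaplan–Meier analyses, and a win ratio with mortality first is a pre-specified sensitivity analysis. A decedent can also beat a survivor by design, through better function before death: in the simulation 17% to 20% of such wins remain after the repair. Ranking function above survival is a legitimate choice in a palliative trial.

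A reader might also suppose that 30% or 40% of patients score zero on both tiers, which would make the effect much larger. Both shares exceed the 22.9% limit set by the planning figures. Nor does eligibility select such a group: one Group 2 criterion suffices, and it can be slow walking, dyspnoea at rest, or inability to wash on 3 of 7 days.

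Other points stand in part. The fallback applies only without daily data and does not say that both must be alive. The value 8 has a use in the secondary PGA model. The unconditional statement concerns longitudinal data and also mentions carrying the last observation forward. An analysis plan not shown may settle pairs without a common visit. None of this reconciles the two sentences on PGA in the primary endpoint itself.

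**Conclusion.** The point holds as an inconsistency in the rules for death in tier 3 and in the washing fallback. The both-alive rule excludes the value 8 that the same paragraph assigns, can reverse the winner of a pair, and leaves deaths before day 10 without a comparison. The fallback can likewise reverse a tier 1 result.

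The size is probably small for PGA, because that tier is reached only after ties on both earlier ones: about 0.2% to 0.3% of all pairs are decedent wins there, under the simulation's assumptions. The fallback matters more where it is used: all decedent wins rise from about 17–20% to 23–25% of pairs of one decedent and one survivor. How often it will be used cannot be told from the article. The limit of 22.9% rests on the planning mean and SD, which the article itself says come from very limited prior data. The case for acting is that the primary result should have one definition, not that a large bias has been shown.

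**What to change.** Set one horizon and one rule for death:

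- Compare PGA at day 30, with 8 for death and the worst living category for severity-related withdrawal. Keep the stated threshold for a winning score. It follows that a survivor in the worst living category ties with a decedent, and two decedents tie.
- Restrict the last common visit to withdrawals judged independent of severity.
- In the washing fallback, count days after death or severity-related withdrawal as zero up to day 30, and say how unrecorded days between the last visit and death are scored.
- State that these rules cover pairs with one death and one completer, and deaths before day 10.
- Keep the both-alive PGA comparison as a sensitivity analysis if wanted.

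The cost is a few sentences and a small programming change, with no new data. Enrolment has ended and the article does not say whether the allocation has been opened, so the choice should be fixed and dated before unblinding, if that has not yet occurred.
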